**Figure 1 fig1:**
[figure not shown]
Study flowchart.

The primary objective is to compare treatment effectiveness using the Numeric Rating Scale (NRS) for radiating pain and the Oswestry Disability Index (ODI) at week 7 relative to baseline. Secondary objectives include assessing changes in NRS for LBP, 100 mm Pain Visual Analog Scale (VAS), Roland-Morris Disability Questionnaire (RMDQ), EuroQol 5-Dimension 5-Level (EQ-5D-5L), Health Information National Trends Survey (HINT-8), Global Perceived Effect (GPE), and Patient Health Questionnaire-15 (PHQ-15) at weeks 3, 7, 12, 19, and 26, alongside economic evaluations for cost-effectiveness. The Kidney Yin Deficiency Pattern Identification Questionnaire (DSKI) scores will be evaluated at week 7. Treatment expectations, intention to use herbal medicine, and disease-related treatment history will also be assessed. Safety will be monitored through adverse event tracking, clinical laboratory tests, vital signs, body weight, and concomitant medication reviews (see Table 1 for study schedule).

**Table 1 tab1:** Study schedule and timelines.

Timelines		Screening	Enrollment allocation	Active treatment post-allocation^2^										Follow-up^1^^,^^2^			
		V0	V1	V2	V3	V4	V5	V6	V7	V8	V9	V10	V11	V12	V13	V14	V15
		−1 W ~ ^3^	0 W^3^	1 W		2 W		3 W		4 W		5 W		7 W	12 W	19 W	26 W
Window period		−14 ~ 0	(baseline)	±4		±4		±4		±4		±4		+14	±7	±7	±7
L-spine CT or MRI^4^		●															
SLR test		●															
Participant eligibility assessment		●															
Consent acquisition		●															
Sociodemographic factors assessment		●															
History taking		●	●														
Review of systems		●												●			
Randomization			●														
Effectiveness and economic evaluation	NRS (lumbago, radiating pain)	●	●					●^5^				●^6^		●	●	●	●
	ODI		●					●^5^				●^6^		●	●	●	●
	100 mm Pain VAS (lumbago, radiating pain)^1^		●											●	●	●	●
	RMDQ		●											●	●	●	●
	EQ-5D-5L		●					●^5^						●	●	●	●
	HINT-8		●					●^5^						●	●	●	●
	GPE							●^5^						●	●	●	●
	PHQ-15		●											●	●	●	●
	Kidney Yin Deficiency Pattern Identification		●											●			
	Economic evaluation^5^		●					●^5^				●^6^		●	●	●	●
	Time costs^5^							●^5^									
	Productivity loss costs^5^		●					●^5^						●	●	●	●
	Treatment expectation scale		●														
	Intention to Choose Herbal Medicine Treatment		●											●			
Safety assessment	Vital signs^1^	●	●					●^5^						●	●	●	●
	Lab tests^7^	●^7^												●^7^			

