	Anthropometric measurements	●												●			
	Concomitant medication review^8^	●	●					●				●		●	●	●	●
	Adverse effect assessment^9^			●		●		●		●		●		●	●	●	●
Treatment compliance assessment^10^				▲^11^		▲^11^		▲^11^		▲^11^		▲^11^		▲^11^			
Experimental group^11^			■		■ (10D)			■ (20D)									
Control group^12^				▲	▲	▲	▲	▲	▲	▲	▲	▲	▲				

1 Follow-up visits at weeks 12, 19, and 26 may be conducted via telephone surveys if in-person visits are impractical. In such cases, vital signs and VAS measurements were omitted.

2 Missing follow-up questionnaires (including telephone surveys) due to a participant’s missed visit will not be considered a protocol violation.

3 For the experimental group, weeks −1 and 0 visits were conducted on the same day. For the control group, weeks −1, 0, and 1–1 visits can were conducted on the same day.

4 Lumbar spine CT or MRI examination results, whether performed at the current institution or other hospitals, may be used if previously acquired.

5 At week 3, the assessment of the NRS, VAS, ODI, EQ-5D-5L, HINT-8, GPE, healthcare utilization costs/time survey, time–cost evaluation, productivity loss, and vital signs may have been conducted concurrently with the day 20 visit for the intervention group. For the control group, these assessments will be performed at week 3–1, or week 3–2 if not completed at week 3–1.

6 NRS, ODI assessments, and medical cost surveys at week 5 will be conducted via telephone survey.

7 Participants will undergo blood and urine tests at weeks −1 and 7. They would be required to visit after an 8-h fasting period on the day prior to blood collection for the tests. Retesting for abnormal results may be performed at the discretion of the investigator. However, for week −1 clinical laboratory tests, the results from tests conducted within 14 days of the screening visit can be substituted. The specific test items were as follows: (a) blood test items: WBC, RBC, neutrophils, lymphocytes, monocytes, eosinophils, basophils, MCV, MCH, MCHC, hemoglobin, hematocrit, platelet count, total protein, albumin, ALT, AST, ALP, total bilirubin, gamma GT, uric acid, BUN, creatinine, BUN/creatinine ratio, serum glucose, PT, aPTT, ESR, and CRP. (b) Urine Test Items: specific gravity, pH, protein, glucose, ketones, urobilinogen, bilirubin, blood, nitrite, WBC (leukocytes). For female participants, urine HCG screening was performed at week −1.

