#### Analysis of efficacy endpoints

2.7.2

1) Primary efficacy endpoint

Changes in Numeric Rating Scale (NRS) for radiating pain and Oswestry Disability Index (ODI) from baseline to week 7 will be analyzed using a Linear Mixed Model, with group as a fixed factor and relevant baseline covariates. Missing data will be handled via Mixed Model for Repeated Measures (MMRM), with sensitivity analyses using ANCOVA on datasets imputed by multiple imputations (MI) and Last Observation Carried Forward (LOCF).

2) Secondary efficacy endpoints

Changes in NRS for low back pain, 100 mm Pain Visual Analog Scale (VAS), Roland-Morris Disability Questionnaire (RMDQ), EuroQol 5-Dimension 5-Level (EQ-5D-5L), Health Information National Trends Survey (HINT-8), Global Perceived Effect (GPE), Patient Health Questionnaire-15 (PHQ-15), economic measures, and Kidney Yin Deficiency Pattern Identification Questionnaire (DSKI) scores will be analyzed using a Linear Mixed Model with baseline covariates. Missing data will be managed via MMRM, with ANCOVA sensitivity analyses using MI and LOCF. Non-inferiority testing, with margins of −1.75 (NRS) and −10 (ODI), will be conducted if superiority is not achieved, considering herbal medicine non-inferior if the 95% confidence interval lower bound does not exceed these margins.

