#### Cost-effectiveness analysis

2.7.4

Economic evaluation will adopt a societal perspective, using a micro-costing approach to compare intervention and control groups over the follow-up period. The Incremental Cost-Effectiveness Ratio (ICER) will be calculated as the cost difference (ΔC) divided by the Quality-Adjusted Life Years (ΔE) difference from EQ-5D-5L scores. Costs include direct medical (e.g., procedures, hospitalization), direct non-medical (e.g., transportation), and indirect costs (e.g., productivity loss). Non-parametric bootstrapping (1,000 replications) will estimate ICER confidence intervals, presented on a Cost-Effectiveness Plane, with a Cost-Effectiveness Acceptability Curve illustrating cost-effectiveness probabilities across willingness-to-pay thresholds.

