#### Missing value management

2.7.5

Missing data for primary and secondary outcomes will be managed using LOCF imputation, selected for its conservative approach in estimating treatment effects post-dropout, assuming stable participant conditions after the last observation, ensuring robust and interpretable efficacy results.

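### Carrying the last value forward does not suit costs collected over unequal survey gaps, and a change in time costs cannot be computed from the schedule

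*Protocol article*

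**What the plan says.** The Methods part of the Abstract counts economic evaluation measures among the secondary outcomes. Section 2.7.2, under secondary efficacy endpoints, opens its list with changes in the named outcomes and ends it with "economic measures, and Kidney Yin Deficiency Pattern Identification Questionnaire (DSKI) scores will be analyzed using a Linear Mixed Model with baseline covariates". EQ-5D-5L has its own entry in that list, so the economic measures are most naturally the cost rows of Table 1.

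On missing data the article says two things. Section 2.7.2: "Missing data will be managed via MMRM, with ANCOVA sensitivity analyses using MI and LOCF". Section 2.7.5: "Missing data for primary and secondary outcomes will be managed using LOCF imputation", justified by "assuming stable participant conditions after the last observation". The second statement exempts no outcome.

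Section 2.7.4 describes a separate economic evaluation, "using a micro-costing approach to compare intervention and control groups over the follow-up period". Its ICER has the cost difference as numerator and 1,000 bootstrap replications for its interval. It names no method for missing costs.

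Table 1 schedules the economic survey at weeks 0, 3, 5, 7, 12, 19 and 26. The week 5 contact is by telephone: "NRS, ODI assessments, and medical cost surveys at week 5 will be conducted via telephone survey". Productivity loss is collected at weeks 0, 3, 7, 12, 19 and 26. Time costs have one mark, at week 3. The recall period of the cost questions is not stated.

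**The concern.** A pain or disability score describes a state at a visit. A cost describes spending over a period. Rules written for scores therefore do not transfer to costs without change.

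Two things follow if the text is applied as written. First, a mixed model of changes gives one contrast per visit, whereas section 2.7.4 needs a cost over the whole follow-up. For an item with a single measurement and no baseline it gives nothing. Second, carry-forward copies the spending of one period into later periods of different length and different treatment phase. A patient's condition may be stable while spending drops sharply once treatment ends.

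Cost-effectiveness is one of the trial's stated aims, and some loss is expected: section 2.3 anticipates 15% attrition (Table 2 says 10%), and footnote 2 of Table 1 does not count missed follow-up questionnaires as protocol violations. If LOCF-filled amounts entered the cost difference, its size could depend on when patients were lost and on whether the arms lost patients at different rates.

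**Working it through.** The article states no cost figure, so there is none to reproduce.

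**1. Survey gaps (Table 1).** Economic survey: 3, 2, 2, 5, 7 and 7 weeks, sum 26. Productivity loss: 3, 4, 5, 7 and 7 weeks, sum 26.

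**2. Does change scoring bias the arm contrast?** Regress (Y − B) on group and baseline cost B. Subtracting B shifts only the coefficient of B by −1; the group coefficient is the same as for Y. A simulation confirms this. Its inputs are all assumed: 33 per arm, 4,000 runs, gamma-distributed costs with mean 100 per week, a 4-week baseline recall and a true difference of 10 per week. At week 26 the true contrast is 10 × 7 = 70. The adjusted raw cost gives 70.4, the adjusted change 70.4 and the unadjusted change 70.7. There is no bias, but this is a single-visit contrast. The cost over follow-up is a different quantity: 10 × 26 = 260 in truth, 260.3 when simulated totals are summed.

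**3. Time costs.** One measurement at week 3 and none at week 0: neither a change nor a repeated-measures model can be computed. Raw week 3 amounts can be compared between arms.

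**4. LOCF for one patient, constant weekly cost.** Assumption: each survey covers the time since the previous one. Weeks credited = weeks observed + (last gap × number of missed surveys).

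| Last seen | Weeks credited | Share of 26 |
|---|---|---|
| Week 3 | 3 + 5 × 3 = 18 | 69% |
| Week 5 | 5 + 4 × 2 = 13 | 50% |
| Week 7 | 7 + 3 × 2 = 13 | 50% |
| Week 12 | 12 + 2 × 5 = 22 | 85% |
| Week 19 | 19 + 1 × 7 = 26 | 100% |

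**5. LOCF for one patient, spending falls after week 5.** Let weekly cost be 1 up to week 5 and r afterwards (r is an assumption). For a patient last seen at week 5, the LOCF total is 13 and the true total is 5 + 21r.

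- r = 1: 13 / 26 = 50%
- r = 0.2: 13 / 9.2 = 141%
- r = 0.1: 13 / 7.1 = 183%

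The error can thus go either way.

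**6. Trial level.** The simulation of step 2 is used, with patients lost after week 7 and constant expected weekly cost. The benchmark is the complete-data total in the same simulated trials.

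- True difference, 15% lost in each arm: 249.6 with complete data, 231.9 with LOCF. Shrinkage is (249.6 − 231.9) / 249.6 = 7.1%. By formula: 0.15 × 13/26 = 7.5%. (249.6 rather than 260 is simulation noise, so the two methods are compared on the same data.)
- No true difference, 10% versus 20% lost: 0.1 with complete data, −128 with LOCF. By formula: (0.20 − 0.10) × 13 × 100 = 130, which is 5% of the 26-week cost of 2,600.

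**The case against.** The strongest reply is that the cost comparison already has its own section. Section 2.7.4 compares costs over follow-up with a bootstrap and uses no change scores. Section 2.7.2 makes LOCF a sensitivity method only, and section 2.7.5 argues for LOCF in terms of treatment effects and efficacy. Nothing states that LOCF-filled costs enter the ICER. GPE, which also has no baseline, stands in the same list of changes, so the sentence may be loose condensation rather than an instruction for every item.

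Much of this stands. A reader might infer that the planned cost comparison is wrong as it is. The article does not support that: change scoring with baseline cost as covariate leaves each visit's contrast intact, and the ICER is defined on a cost difference. A reader might also infer that time costs cannot be compared at all; only their change is impossible. A third tempting inference is that carry-forward multiplies trial treatment costs, because all three herbal supplies are issued by day 20. That would require the surveys to capture trial treatment, whereas prescribed packs and treatment sessions are recorded directly in the case report form and could be costed from there.

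The reply does not remove the point. Economic measures are secondary outcomes, 2.7.5 covers secondary outcomes without exemption, and no other missing-data rule is stated for the cost totals. This is a stated rule that does not fit the data, not a detail left to a fuller document.

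**Conclusion.** The point holds in a limited form. LOCF is unsuitable for costs and would distort the cost difference if section 2.7.5 governs or if filled amounts feed the ICER. The article leaves this open, because 2.7.2 and 2.7.5 disagree on the status of LOCF. The change-score model is not biased for costs but answers a different question from 2.7.4, and for time costs a change is undefined.

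For one patient last seen at week 5, the LOCF total is 50% of the truth at constant spending, and 141% or 183% if later spending falls to 20% or 10%. These figures describe a single dropout and should not be read as the error in the trial result. That error is nearer 7% shrinkage of a true difference, or a false difference of about 5% of total cost, in the two scenarios simulated. All sizes rest on the assumption that each survey covers the time since the last; a fixed short recall would change them. The trial-level figures also rest on the assumed cost distribution and loss pattern. The primary outcomes are not affected.

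**What to change.** - Section 2.7.2: remove economic measures from the list of outcomes analysed as changes.
- Section 2.7.5: exempt costs from LOCF, and reconcile this section with 2.7.2 on whether LOCF is the main method or a sensitivity analysis.
- Section 2.7.4: state that the cost comparison and the ICER numerator use each patient's total over weeks 0 to 26, summed over survey periods. Missed periods are filled by multiple imputation (for example within arm), and the difference in totals is given with a bootstrap confidence interval.
- Compare time costs between arms as raw week 3 amounts.

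The cost is a change of wording and slightly more imputation work. No further data are needed.

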### Outcome measures

2.6

This study used a comprehensive set of outcome measures to evaluate the effectiveness and safety of the interventions. All patient-reported outcomes were assessed at specific visits throughout the study.

(1) NRS scores for pain intensity (low back and radicular pain).

At weeks −1 (baseline), 0, 3, 5, 7, 12, 19, and 26, participants will assess their low back pain and radiating leg pain over the past week using an 11-point Numeric Rating Scale (NRS), ranging from 0 (no pain) to 10 (worst pain imaginable), selecting the number that best reflects their current discomfort level.

(2) Oswestry disability index.

At weeks 0, 3, 5, 7, 12, 19, and 26 visits, participants will complete the ODI (19) questionnaire by providing answers to each question.

(3) VAS score for pain intensity (low back and radicular pain)

At weeks 0, 7, 12, 19, and 26, participants will use a 100 mm Pain Visual Analog Scale (VAS) (20) to quantify their LBP experienced over the past week. Participants will indicate their current pain level by marking a point on a 100 mm Visual Analog Scale (VAS), ranging from “no pain” to “worst pain imaginable”.

(4) Roland-Morris disability questionnaire (RMDQ)

At weeks 0, 7, 12, 19, and 26, the participants will complete the Roland-Morris Disability Questionnaire (RMDQ) (21) by answering each question.

(5) EuroQol-5 dimension-5 level (EQ-5D-5L)

At Weeks 0, 3, 7, 12, 19, and 26, the participants will complete the EQ-5D-5L (22) questionnaire by responding to each question.

(6) Health-related quality of life instrument with eight items (HINT-8)

At weeks 0, 3, 7, 12, 19, and 26, participants will complete the HINT-8 questionnaire (23). Participants will assess their health status over the past week by selecting one of four response levels for each question, ranging from 1 (e.g., “not at all” for climbing stairs or “not at all depressed” for depression) to 4 (e.g., “unable to climb” or “always depressed”).

(7) Global perceived effect (GPE)

At weeks 3, 7, 12, 19, and 26, participants completed the Global Perceived Effect (GPE) questionnaire (24) by providing answers to each question.

(8) Patient health questionnaire-15 (PHQ-15)

At weeks 0, 7, 12, 19, and 26, participants will complete the Korean version of the Patient Health Questionnaire-15 (PHQ-15). This tool, a 15-item condensed version (25) developed by Kroenke et al. from Spitzer et al.’s PHQ (26), assesses general health status and subjective somatic symptoms.

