(9) Kidney Yin deficiency pattern identification questionnaire score (DSKI)

At weeks 0 and 7, participants will complete the Kidney Yin Deficiency Pattern Identification Questionnaire (DSKI) (27) to assess the Kidney Yin Deficiency Pattern, a diagnostic construct in Korean traditional medicine characterized by symptoms such as lower back pain, fatigue, night sweats, dry mouth, and insomnia, reflecting an imbalance in yin energy essential for bodily nourishment and cooling. The DSKI quantifies these symptoms through a standardized set of questions, with scores indicating the severity of the deficiency pattern. This measure is relevant to the study as it evaluates the impact of traditional alternative therapies on a key diagnostic pattern associated with lumbar disc-related radiating pain.

(10) Intention to choose herbal medicine.

At weeks 0 and 7, participants were asked about their perceived need for herbal medicine treatment in their current condition.

(11) Treatment expectation scale.

At the initial visit, participants will rate their expectations of symptom relief from herbal medicine and acupuncture treatments on a 9-point Likert scale (1 = not at all, 5 = somewhat, 9 = very much).

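### For DSKI, RMDQ, PHQ-15 and VAS nothing is scheduled between baseline and week 7, so the stated MMRM and LOCF do little for participants lost before week 7, and agreement between the two would not show robustness

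*Protocol article*

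**What the plan says.** Section 2.7.2, under secondary efficacy endpoints, sets one rule for all scales, DSKI included. Change is analysed by a linear mixed model with baseline covariates, and "Missing data will be managed via MMRM, with ANCOVA sensitivity analyses using MI and LOCF". Section 2.7.5 names LOCF for primary and secondary outcomes, calls it conservative, and justifies it as "assuming stable participant conditions after the last observation".

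Section 2.6 gives the schedules:

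- RMDQ: "At weeks 0, 7, 12, 19, and 26, the participants will complete the Roland-Morris Disability Questionnaire (RMDQ".
- PHQ-15: "At weeks 0, 7, 12, 19, and 26, participants will complete the Korean version of the Patient Health Questionnaire-15 (PHQ-15".
- VAS: "At weeks 0, 7, 12, 19, and 26, participants will use a 100 mm Pain Visual Analog Scale (VAS".
- DSKI: "At weeks 0 and 7, participants will complete the Kidney Yin Deficiency Pattern Identification Questionnaire (DSKI".

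The Table 1 grid agrees with all four. Two places do not. The objectives paragraph in section 2.1 puts VAS, RMDQ and PHQ-15 in a list that ends "and Patient Health Questionnaire-15 (PHQ-15) at weeks 3, 7, 12, 19, and 26", and Table 1 footnote 5 includes VAS among the week-3 assessments. NRS and ODI, by contrast, are scheduled at weeks 3 and 5 throughout.

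**The concern.** An MMRM deals with dropout by borrowing from a participant's earlier post-baseline scores on the same scale. Where no such score is scheduled before the time point of interest, it has nothing to borrow. LOCF has the same difficulty: the last observation is the pre-treatment one, so the method imputes no change instead of a state reached on treatment.

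Loss before week 7 may be informative. Section 2.8 lists arm-specific adherence thresholds among the grounds for removal and makes later assessment optional. If early response drives loss differently in the two arms, the main and LOCF results can both be wrong, and a reader could take their agreement as reassurance. The week-3 and week-5 NRS and ODI would help to predict the missing scores, but a model for one scale at a time does not use them.

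**Working it through.** **Plan's own figure.** The article states no figure on this point except attrition: 15% in the text of section 2.3 and 10% in Table 2.

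**1. What each method does for a participant lost for good before week 7 (Table 1 schedule)**

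| Scale | Post-baseline scores | Model of change | LOCF |
|---|---|---|---|
| DSKI | week 7 only | no repeated measures; complete-case ANCOVA | baseline carried, change 0 |
| RMDQ, PHQ-15, VAS | weeks 7, 12, 19, 26 | no record | baseline carried, change 0 |

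The LOCF column assumes that baseline may be carried forward, which the article does not state. If it may not, LOCF imputes nothing for these participants.

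**2. How many.** 74 × 0.10 = 7.4 and 74 × 0.15 = 11.1, so about 7 to 11. This is an upper limit, because it places all attrition permanently before week 7, while follow-up runs to week 26.

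**3. Bias in the between-arm difference.** Let both arms lose a share p. Let t be the true effect (herbal minus control, negative favouring herbal medicine) and D the same difference in true mean change among lost participants. Ignoring baseline adjustment:

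- The completers' difference is (t − pD)/(1 − p), so the complete-case bias is p/(1 − p) × (t − D).
- With zero change imputed, the difference is t − pD, so the bias is −pD.

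At p = 0.15, p/(1 − p) = 0.176. In SD units, with the section 2.3 target of 0.5 SD as a benchmark and D assumed:

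| t | D | Complete-case bias | Baseline-carried bias | Direction |
|---|---|---|---|---|
| 0 | +0.5 | −0.09 | −0.08 | same |
| −0.5 | +0.5 | −0.18 | −0.08 | same |
| −0.5 | −0.25 | −0.04 | +0.04 | opposite |
| −0.5 | −0.5 | 0 | +0.08 | LOCF only |

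With equal loss, the signs must match only when t = 0. When t is not 0, they oppose for any D between 0 and t.

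**4. Simulated size, equal loss and t = 0.** Assumptions: about 15% lost per arm, at random in control and after poor early response in the herbal arm; correlation 0.4 to 0.7 between the early score and week-7 change; dropout slopes 1 and 2; both arms improving 0.6 SD.

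- With 37 per arm: complete-case bias 0.03 to 0.11 SD, baseline-carried 0.04 to 0.12 SD.
- Large-sample version: 0.05 to 0.14 and 0.05 to 0.12 SD.
- Every bias favours herbal medicine. Imputation using the early score leaves 0.01 SD or less.

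**5. Unequal loss and a true effect.** Assumed true difference −1.5 points, residual SD 4, loss 20% herbal and 5% control:

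| Reason for loss | Complete case | Baseline carried | Imputation with early score |
|---|---|---|---|
| At random | −1.49 | −0.59 | −1.49 |
| Poor early response | −1.95 | −0.96 | −1.51 |
| Good early response | −1.07 | −0.26 | −1.51 |
| Strongly on the unseen week-7 change | −2.38 | −1.30 | −2.08 |

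In rows two and four the two planned methods bracket the truth. In row three both understate the effect. Row four marks the limit of the remedy: early scores recover only what they predict.

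**The case against.** A reader might infer that whenever loss depends on early response, the MMRM and LOCF results err together and confirm each other. The documents do not support that. It needs particular loss rates, mechanisms and effects. If the same mechanism acts in both arms at equal rates, the complete-case bias is about zero. With a 0.5 SD effect and herbal-only informative loss at 20% against 10%, the biases were −0.11 and +0.08 SD (correlation 0.6, slope 1). If loss depends only on arm and baseline, the complete-case model is unbiased.

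Four further points stand:

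- Multiple imputation is already a planned sensitivity analysis, and its variables may be in the fuller plan. The article neither names nor excludes the early NRS and ODI. The choice matters, because imputation from arm and baseline alone would add almost nothing to the main model.
- Participants who miss week 7 but return at week 12 stay in the RMDQ and PHQ-15 models, and in the VAS model if seen in person. Section 2.8 also permits assessment after treatment stops.
- If the week-3 listing in section 2.1 governs, the gap closes for RMDQ, PHQ-15 and VAS, leaving only DSKI.
- The bias is small beside chance. With 37 per arm the unadjusted standard error is √(2/37) = 0.23 SD.

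These points limit the size of the problem. They do not restore what the stated MMRM and LOCF are meant to do for a participant who has only a baseline score.

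**Conclusion.** The point holds as a modest one about secondary endpoints. For DSKI the stated MMRM is complete-case ANCOVA on any reading of the schedule. For RMDQ, PHQ-15 and VAS, on the Table 1 and section 2.6 schedule, anyone lost for good before week 7 contributes nothing to the model. For all four scales, LOCF could supply only the pre-treatment score, so the section 2.7.5 rationale of a conservative, stable on-study state does not hold for these participants.

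Both methods can be biased if loss depends on early response differently by arm. The biases may agree or oppose according to the loss rates and the true effect. With equal loss and no true difference they share a direction, about 0.03 to 0.14 SD under the assumed scenarios. So agreement between MMRM and LOCF is not evidence of robustness, but agreement in error is not assured either. The 7 to 11 participants are a ceiling. The primary endpoints, NRS for radiating pain and ODI, have week-3 and week-5 scores and are unaffected.

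**What to change.** 1. Reconcile the week-3 listing of VAS, RMDQ and PHQ-15 in the section 2.1 objectives, and of VAS in Table 1 footnote 5, with the Table 1 grid and section 2.6.
2. Describe the DSKI analysis as ANCOVA of the week-7 score or change, adjusted for baseline.
3. For DSKI, RMDQ, PHQ-15 and VAS at week 7, use the already planned multiple imputation followed by ANCOVA. The imputation model should contain arm, the scale's baseline score, the week-3 and week-5 NRS and ODI, and later scores on the scale where present.
4. Drop LOCF for these four scales where it would carry the baseline score, and limit the section 2.7.5 rationale accordingly.

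The cost is a change of wording and a slightly more complex analysis of secondary endpoints. No new data are needed, since the early NRS and ODI are already scheduled.

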### Sample size calculation

2.3

The target sample size for this PRCT was rooted on a previous research (17). The required sample size was determined by calculating the minimum number of participants needed to detect a clinically meaningful difference between the intervention and control groups, specifically for the primary outcome measure, using a superiority design. The effect size (Cohen’s d) was estimated at 0.5, representing a moderate difference we aimed to detect. Assuming an alpha level (*α*) of 0.05 (two-sided) and a statistical power (1 − *β*) of 80% (0.80), the required number of participants per group (n) was calculated using the formula for comparing two independent means: *n* = 2 × *δ*2(Zα/2 + Zβ)2 × *σ*2, where Zα/2 and Zβ are the standardized normal deviates corresponding to the significance level and power, σ is the estimated standard deviation, and δ is the minimum clinically important difference. We estimated the standard deviation (σ) to be 10 points and set the minimum detectable difference (δ) to be 5 points on the primary outcome scale. Accounting for an anticipated 15% attrition rate, the total required sample size was adjusted from N_calculated_ to N_final_ to ensure adequate power at the study’s conclusion, resulting in a target enrollment of 74 participants (37 per group). Target sample sizes are listed in Table 2. This trial is powered for a superiority outcome, but a secondary, exploratory non-inferiority (NI) analysis is planned to assess the comparative effectiveness or safety of the intervention if the superiority hypothesis is not met. This approach is clinically relevant for pragmatic trials, evaluating whether the intervention is “not worse” than the control within a predefined NI margin (*Δ*). However, the sample size of 74, calculated for superiority, is likely insufficient for a definitive NI trial, as NI analyses typically require larger samples to ensure the confidence interval of the treatment difference lies within Δ. To address this, the manuscript will clarify that the NI analysis is exploratory and hypothesis-generating, underpowered for this endpoint, and will report the NI margin and two-sided 95% confidence interval for the primary outcome difference.

**Table 2 tab2:** Target sample size of the study.

Category	Control group	Intervention group	Total participants
Efficacy evaluable cases	33	33	66
Total sample size (incl. 10% dropout)	37	37	74

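### The ODI non-inferiority margin of 10 is twice the 5-point difference used for planning, has no rationale, and does not fit the statement that the non-inferiority analysis is underpowered

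*Protocol article*

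**What the plan says.** Section 2.3 (Sample size calculation) explains its formula by saying that "δ is the minimum clinically important difference". It then says "We estimated the standard deviation (σ) to be 10 points" and that the authors "set the minimum detectable difference (δ) to be 5 points on the primary outcome scale". The same paragraph describes the effect size as one that "was estimated at 0.5, representing a moderate difference we aimed to detect". One quantity, 5 points, thus carries two labels, and the scale is not named.

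The primary outcomes are change to week 7 in NRS for radiating pain and in ODI (Section 2.7.2). Section 2.6 gives the NRS range as 0 to 10.

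Section 2.7.2 then provides: "Non-inferiority testing, with margins of −1.75 (NRS) and −10 (ODI), will be conducted if superiority is not achieved". It goes on to give a rule under which herbal medicine is considered non-inferior, based on one limit of the 95% confidence interval. The article gives no reason for either margin.

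Section 2.3 says that "the NI analysis is exploratory and hypothesis-generating, underpowered for this endpoint", that 74 participants are probably too few for a definitive non-inferiority trial, and that the margin and the two-sided 95% interval will be reported. The Discussion repeats that the sample size limits this analysis. The Abstract announces non-inferiority testing without the exploratory label.

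**The concern.** A non-inferiority margin is the largest loss one is prepared to disregard. It should not normally exceed the smallest difference that the same plan regards as important. Here Section 2.3 uses 5 points and Section 2.7.2 tolerates 10, and nothing links the two.

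Two things are at stake. First, the rule can yield a statement of non-inferiority although the data do not exclude a loss well above δ. Second, readers are told that the test is hard to pass at this sample size. On the plan's own margin and SD it is easy to pass, so a positive result would look more persuasive than it is.

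**Working it through.** **Inputs.** δ = 5, SD = 10, two-sided α = 0.05 and 80% power (Section 2.3); 33 evaluable per arm (Table 2); ODI margin 10 (Section 2.7.2). I count a deficit as herbal medicine having the worse ODI, and take non-inferiority to mean that the upper 95% limit of the deficit is below the margin. The printed rule does not define the sign of the difference. That is a separate wording matter.

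**Which scale.** An SD of 10 is impossible on a 0 to 10 scale, so δ = 5 with SD 10 cannot refer to the NRS. Of the two primary outcomes, only the ODI remains.

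**The plan's own sample size.** n per arm = 2(1.960 + 0.842)² × 10²/5² = 62.8, so 63, against 33 in Table 2. The stated 74 is not reproduced. That is a separate defect. Below I take 33 per arm as given.

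**Margin against δ.** 10/5 = 2.0. Margin against SD: 10/10 = 1.0.

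**Precision.** SE = 10 × √(2/33) = 2.46. With t(64 df) = 1.998 the half-width is 1.998 × 2.462 = 4.92. Non-inferiority is met for any observed deficit below 10 − 4.92 = 5.08, slightly above δ.

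**Probability of declaring non-inferiority**, Φ((margin − true deficit)/SE − 1.998), margin 10:
- no true difference: Φ(4.06 − 2.00) = 98%
- herbal medicine truly 5 worse: Φ(2.03 − 2.00) = 51% (53% with 1.960 in place of 1.998)

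With a margin of 5:
- no true difference: Φ(2.03 − 2.00) = 51%
- herbal medicine truly 5 worse: 2.5%, the nominal one-sided error

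**Sample size for 80% power at no difference.** Margin 10: 2 × 2.802² × 100/100 = 15.7, so 16 per arm. Margin 5: 63 per arm. The statement that 74 participants are too few agrees with the second margin and not with the first.

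**Sensitivity to the SD** (assumed values other than 10; margin 10, 33 per arm, normal quantile 1.960):

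| SD | No true difference | Truly 5 worse |
|---|---|---|
| 8 | 99.9% | 72% |
| 10 | 98% | 53% |
| 12 | 92% | 39% |
| 15 | 77% | 27% |
| 18 | 62% | 20% |

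Power at margin 10 falls below 80% once the SD exceeds 10/(2.802 × √(2/33)) = 14.5.

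**The case against.** The strongest defence is the label. Section 2.3 calls the analysis secondary and exploratory and promises the margin and the interval, so a reader would see any loss that is not excluded. The primary superiority analysis is untouched. This stands, and it limits the severity. It does not explain a margin of 10. The declarative rule in Section 2.7.2 and the mention in the Abstract also do not carry the label.

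Second, 5 may be only a planning effect. The sentence that sets it speaks of a detectable difference, and 5 is exactly 0.5 × 10. A reader might infer that the plan knowingly accepts a clinically meaningful loss. The documents do not establish that: the link to the ODI is by elimination, and the clinical label appears only in the explanation of the formula. On the planning-effect reading, however, that label is wrong and the margin still needs a reason.

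Third, the SD of 10 comes from a calculation that does not reproduce. If the true SD were above about 14.5, calling the analysis underpowered would be correct even at margin 10. This stands against any claim that non-inferiority is nearly certain whatever the SD. The contradiction is with the SD that the plan itself states.

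Two further inferences should be resisted. One is that the NRS margin of 1.75 is also too wide: the article gives no NRS δ or SD, so this cannot be judged. The other is that results both significantly inferior and non-inferior would be common. The trigger does not rule them out, but at SD 10 they need an observed deficit between 4.92 and 5.08.

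**Conclusion.** The point holds at moderate severity. Sections 2.3 and 2.7.2 use 5 and 10 points on what can only be the same scale, and the article does not reconcile them. At SD 10 and 33 per arm, the rule would declare non-inferiority about half the time when herbal medicine is truly 5 points worse. Over assumed SDs of 8 to 18 this is about 72% to 20%, well above the 2.5% that a margin of 5 would give. The statement about low power does not match the stated margin and SD. It would match a margin of 5.

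The result rests on the ODI link by elimination, on 33 evaluable per arm, and on reading the decision rule in its sensible direction. It does not show that the primary analysis is compromised, that 10 points could never be justified, or that the NRS margin is wrong.

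**What to change.** 1. In Section 2.3, name the scale to which δ = 5 and SD = 10 apply, and say whether δ is a clinically important difference or only a planning effect.
2. Preferably remove the declarative rule from Section 2.7.2 and report the two-sided 95% confidence interval for the difference only, which fits the exploratory label. Section 2.3's promise to report a margin and the Abstract's mention of non-inferiority testing should then be brought into line. Otherwise, set the ODI margin no larger than 5 and state the resulting power: about 51% at 33 per arm and SD 10.
3. Correct the statement on power in Section 2.3, and the matching remark in the Discussion, to fit the choice made. If only the interval is reported, give the expected half-width instead (about 4.9 points at SD 10).
4. If any non-inferiority rule remains, allow no such claim when the interval shows herbal medicine significantly worse.

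The cost is wording in the protocol and any analysis plan. The downside is that a non-inferiority claim becomes harder to reach or is no longer made. With a margin of 5, 80% power would need 63 evaluable per arm, which this trial does not plan. Recruitment is under way and the trial is open-label, so the change should be made before outcomes are compared between arms.
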